between the patient and their PCP, which has also been demonstrated to reduce healthcare costs in these patients.

*To improve access to care for rural populations, healthcare decision makers need new models of service delivery that are based on the principles of chronic disease management, and respond to the needs of rural patients and complement primary care.*

**The Patient with Multiple Chronic Diseases:** Patients with one chronic disease often have, or are at risk for, another chronic disease. For example, diabetes and chronic kidney disease are risk factors for ischemic heart disease, and many patients with ischemic heart disease will face a future diagnosis of heart failure. This group of complex patients represents a substantial challenge to healthcare resources; we have found that compared to patients with only one chronic disease, these patients present with a greater number of primary care and specialist visits, acute care hospital days, and redundant duplicate laboratory tests. The following scenarios highlight the challenges faced by patients with multiple diseases living in urban and rural areas:

- **Urban scenario:** Mrs S lives in Vancouver and was diagnosed with diabetes 10 years ago. She attends a diabetes teaching centre in which she consults with an endocrinologist, nurse and dietitian. She also has impaired renal function and attends her local renal clinic where she sees a nephrologist, a second nurse and a second dietitian. Recently, Mrs S had a myocardial infarction and was referred to the hospital cardiac rehabilitation program, where she will consult with a cardiologist, a third nurse, a third dietitian and an exercise specialist. While each clinic is aware of [name] co-morbidities, her care is not coordinated: each discipline (endocrine vs renal vs cardiac rehab) is focused on its own disease outcomes and prognosis. The clinics are not located in physical proximity and there is no opportunity for sharing medical records. This scenario results in an excessive burden of time and resource allocation, in parallel with potential for confusion among the patient and healthcare providers, and duplication of medical tests. The overall effect is healthcare inefficiencies and risk of serious mistakes, owing to a lack of a shared patient care plan.

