
**Inclusion Criteria:** Men and women with two or more of the five targeted chronic diseases; daily Internet access (home, work or other environment) by any means (such as personal computer, personal data assistant or smartphone); over 19 years of age; and able to read, write and understand English without difficulty.

**Exclusion Criteria:** Patients with significant co-morbidities (excluding the five targeted conditions these include HIV, uncontrolled metabolic/endocrine disorders, prior stroke or other conditions affecting cognitive abilities to

provide consent and participate, alcohol/drug addiction) that may interfere with effective management; patients who have scheduled surgical procedures; and patients who are unable to provide informed consent.

Detailed records will be kept of all individuals who are screened for the study to clearly define the population from which our study cohort will be derived and to ensure our reporting will follow the CONSORT guidelines.

**Study Outcomes:** *The primary outcome will be the difference between the iCDM and usual care groups in hospital admissions from the time of randomization to the end of two years.* Data will be collected by participant self-report and confirmed through access to participant medical records in those who sign the study's Medical Records Release Form. We will also collect data from Provincial Databases hosted by the Population Data BC; Medical Services Plan payment information file, PharmaCare file, hospital separations file and Vital Statistics deaths and clinical deaths on secondary outcomes of healthcare utilization such as length of hospital admissions, emergency room visits, physician/nurse practitioner visits, diagnostic and lab procedures. In addition, secondary outcomes will include patient quality of life, self-management, patient and provider experience, and mortality (see below).

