**Baseline Assessment:** We will collect the following data variables on all consenting participants: social demographics, medical history, current medications, self-management and quality of life, smoking status, alcohol consumption, e-health literacy, and recent diagnostic and lab tests (<6 months). The baseline (and follow-up) assessment will be conducted without the need for the research coordinator to meet with the patient. Data on patient demographics, medical history, current medications, smoking status, and recent diagnostic and lab tests will be abstracted from the patient's physician's/nurse practitioner's medical record and confirmed by telephone with the patient. For all other outcomes we will be using self-administered questionnaires which will be mailed to the patient with a stamped return envelope to mail back. If after two weeks the questionnaires have not been received, the research coordinator will contact the patient by telephone to follow-up. We will create a toll-free number for participants to call the research coordinator to return any messages from the coordinator and ask questions regarding assessment data collection so that participants will not have to incur long-distance phone charges.

**Randomization:** Participants will be stratified by sex and site of recruitment (based on health authority), and then randomized to either usual care or the iCDM using computer-generated variable blocks of 2, 4 and 6 within a web-based randomization system. A research assistant not involved in data collection will access the randomization system using a unique authorization code. The date and time, patient identifiers and randomization codes will automatically be maintained in a transaction file. This same research assistant will be responsible for communicating group assignments to the study participants. Participants will be informed not to discuss their group assignment with the research coordinator responsible for data collection to ensure the study

remains single-blinded. If at the time of being informed of their group assignment, the participant becomes distressed, anxious or upset, the research coordinator will inform the participant that the study psychologist is available to discuss their concerns if they wish.

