## STATISTICAL ANALYSES

We anticipate that 10% of the study population will be lost-to-follow-up at the end of study. Lost-to-follow-up will be defined as those participants who have died, withdrawn from the study or moved out of the province. Every effort will be made to obtain final data on the primary and secondary outcomes from subjects regardless of the extent of study participation to that point. *Lack of compliance to the iCDM will not be a reason for withdrawal from the study.* We will explore differences in baseline variables between those lost-to-follow-up and those who remain in the study.

The primary outcome of hospital admissions between the two groups from baseline to two (dependent variable) years will be modeled using ordered logistic regression with group assignment, age and sex as *a priori* covariates. In the event of potentially clinically relevant differences in baseline factors, we will include these covariates in the model (such as socio-demographics, e-health literacy, depression, and other morbidities). Non-normally distributed continuous variables will be transformed prior to analyses. Residual plots for the primary outcome models will be plotted and assessed for model adequacy. Secondary outcomes between the two groups will be compared using the Pearson Chi-square test for categorical variables and independent samples t-test for continuous variables. All analyses will be governed by intent-to-treat with no group crossovers.

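### Number of target diseases should be an a priori covariate in the primary model, not one admitted only if the arms look different at baseline

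*Protocol*

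**What the plan says.** The Statistical Analyses section states that the primary outcome "will be modeled using ordered logistic regression with group assignment, age and sex as" a priori covariates. Any other covariate has one route in: "In the event of potentially clinically relevant differences in baseline factors, we will include these covariates in the model". The examples given are "such as socio-demographics, e-health literacy, depression, and other morbidities". The section does not say whether the last item covers the five target diseases or only conditions beyond them.

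Three other parts of the Protocol bear on this.

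- The inclusion criteria admit "Men and women with two or more of the five targeted chronic diseases", so participants carry between two and five of them.
- The Baseline Assessment collects "social demographics, medical history, current medications, self-management and quality of life" and more from all consenting participants. Medical history is abstracted from the provider's record and confirmed by telephone.
- The Randomization paragraph stratifies by sex and health authority, not by disease.

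On prognosis, the background section on patients with multiple chronic diseases sets them against people who have a single disease and reports that "these patients present with a greater number of primary care and specialist visits, acute care hospital days, and redundant duplicate laboratory tests". The Abstract adds that people with more than one of these diseases are more likely to develop complications.

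**The concern.** Adjustment in a randomised trial pays off when the covariate predicts the outcome. Observed balance is a poor guide. A strong predictor that happens to be balanced still improves the analysis, while an imbalanced factor with no bearing on admissions adds nothing. The Protocol applies the balance criterion to morbidity, gives no threshold for a clinically relevant difference, and so leaves the final primary model to a judgement made on the trial's own data.

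Disease burden is the most obvious candidate for adjustment. It varies by design, is available from data already planned, and is not controlled by the randomisation. At stake is some power in a trial with little to spare: the Sample Size Determination table gives 0.39 to 0.78 over the tabulated event rates.

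**Working it through.** **Inputs from the Protocol.** 270 completers, taken as 135 per arm (1:1 is assumed; the ratio is not stated). Alpha 0.05, taken as two-sided. A 25% reduction. Usual-care v iCDM rates of 40/30, 50/38, 60/45 and 70/53%. Pilot usual-care rate 32/30 = 1.07 admissions per patient over two years.

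**Assumed, because the Protocol gives no figure.** The mix of 2, 3, 4 and 5 diseases, and the effect of each extra disease on admissions.

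**Step 1: the plan's own power table.** Logistic Wald approximation: power = Φ(|log OR|/SE − 1.96), with SE² = 1/[135·p₁(1−p₁)] + 1/[135·p₂(1−p₂)]. For 40% v 30%: |log OR| = 0.442, SE = √(1/32.40 + 1/28.35) = 0.257, ratio 1.718, power Φ(−0.242) = 0.404. The four rows give 0.404, 0.508, 0.691 and 0.814, against the stated 0.39, 0.55, 0.67 and 0.78. The match is close but not exact. Row 2 becomes 0.542 with the unrounded 37.5%. The residual difference does not affect this point.

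**Step 2: binary logistic simulation at the table's rates.** 6,000 trials per cell, 135 per arm, marginal rates held at the Protocol's values. Models: group alone v group plus disease count; age and sex are not simulated. Simulation error of each power is at most √(0.25/6000) = 0.0065. Entries are power without → with the count.

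| Mix of 2/3/4/5 diseases (%) | OR per extra disease | 40% | 50% | 60% | 70% |
|---|---|---|---|---|---|
| 40/30/20/10 | 1.0 | 0.403→0.402 | 0.514→0.518 | 0.695→0.703 | 0.829→0.825 |
| 40/30/20/10 | 1.3 | 0.398→0.407 | 0.506→0.517 | 0.681→0.699 | 0.824→0.825 |
| 40/30/20/10 | 1.6 | 0.414→0.426 | 0.504→0.527 | 0.679→0.712 | 0.832→0.840 |
| 40/30/20/10 | 2.0 | 0.407→0.453 | 0.503→0.554 | 0.682→0.734 | 0.823→0.848 |
| 40/30/20/10 | 3.0 | 0.406→0.496 | 0.513→0.609 | 0.668→0.778 | 0.822→0.889 |
| 70/20/8/2 | 2.0 | 0.412→0.430 | 0.518→0.544 | 0.673→0.710 | 0.833→0.840 |
| 70/20/8/2 | 3.0 | 0.398→0.444 | 0.512→0.568 | 0.688→0.748 | 0.833→0.857 |

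Up to an odds ratio of 2 the change runs from nothing to about 5 points. About 10 points needs an odds ratio of 3 and a wide mix. With no prognostic value (OR 1.0) the change is under 1 point either way.

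**Step 3: the planned ordered logistic model.** 135 per arm, usual-care mean 1.07, 25% reduction, 1,500 trials per cell. With rate ratios up to 1.5 per extra disease, with or without one higher-risk disease at 1.5 to 2.0, adding disease count alone gains about 0.5 to 7 points. With a rate ratio of 1.0 essentially nothing is lost. Simulation error per power is about √(0.35·0.65/1500) = 0.012, so the low end of the range cannot be told from zero.

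**Step 4: a more favourable case.** Adding both the count and an indicator for the higher-risk disease (3,000 trials per cell, counts capped at 5, gamma frailty with k = 2, rate ratios 1.3–1.5 per disease and 1.5–2.0 for the indicator):

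- mix 40/30/20/10: 0.357→0.403, 0.323→0.375, 0.302→0.387
- mix 70/20/8/2: 0.385→0.409, 0.347→0.389, 0.329→0.383

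These gains, 2.4 to 8.5 points, are an upper guide, because the model is given exactly the two factors that generate the outcome.

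**Step 5: type I error.** Two null runs, without v with the extra terms: 0.054 v 0.056 (12,000 trials) and 0.054 v 0.059 (simulation error about 0.004).

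**The case against.** Several objections have force, and each limits the point.

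- **Prognosis is not documented in this population.** The background comparison is of several diseases with one, and one-disease patients are ineligible. It reports hospital days, not admissions, and gives no effect size. A reader might infer that the Protocol shows burden to drive admissions among participants. It does not; a gradient across two to five diseases is plausible only.
- **Eligibility does not yield a full count.** Screening can stop once two diseases are confirmed. The count has to come from the baseline medical history.
- **The power table is not the whole power statement.** The Protocol also claims power above 0.80 if the pilot clinic's event rate recurs. The lower values in the ordered logistic simulations depend on assumed overdispersion and are not offered as a correction of that claim.
- **The odds ratio moves, but this is not bias.** In Step 4 the treatment log odds ratio was between −0.34 and −0.38 without the disease terms and about −0.40 with them. A reader might call that bias toward no effect. In a randomised trial it is non-collapsibility: the two models estimate different conditional odds ratios, and both give valid tests.
- **Heart failure is not singled out.** One might want it as a separate covariate, but no part of the Protocol identifies it as the target disease with the highest admission risk.
- **Morbidity is not shut out.** It can enter conditionally, and an analysis plan might add detail. The Protocol nevertheless fixes the a priori list and the entry rule itself, so this is a choice made, not one left open.

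**Conclusion.** The point stands as a low-cost improvement, not as an error that invalidates the analysis. The primary model fixes age and sex and leaves disease burden to an imbalance rule, although burden is obtainable for everyone, unstratified and plausibly prognostic.

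The size is about 0 to 7 percentage points of power under assumed rate ratios of 1.0 to 1.5 per extra disease, with or without one higher-risk disease at 1.5 to 2.0. The disease mix and the overdispersion are also assumed. Nothing material is lost if those assumptions fail. A reader might hope that the term would rescue the weaker power scenarios; it does not. For example, at a 50% usual-care rate power is about 0.55 with the term even at an odds ratio of 2 per disease.

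**What to change.** In the Statistical Analyses section, add number of target diseases (2, 3, 4 or more) to age and sex as an a priori covariate, and state that it stays in the model whatever the observed balance. Do not give any single disease its own term on the present evidence. Under Baseline Assessment, state that presence or absence of each of the five target diseases is recorded for every participant, so that the count does not stop at the two needed for entry. Make the change before outcome data are seen by arm.

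The cost is a line of text in each place and one degree of freedom (linear count) or two (three categories). The source, the medical history abstracted at baseline, is already planned.

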**Sample Size Determination:** We have identified a convenience sample of 318 participants as feasible based on our methods of recruitment and study timelines. Based on our current study of a 'virtual cardiac rehabilitation program' in Northern BC which has a reported drop-out rate of 12%, we have set a drop-out rate of 15% due to patient withdrawal, death and moving outside of the province, and will therefore finish with 270 participants. We will collect detailed information on the subjects who withdraw and their reasons for withdrawing. In our pilot combined clinic at St. Paul's Hospital for patients with two or more of cardiovascular disease, diabetes and chronic kidney disease, we observed 32 hospitalizations over a two-year period in the 30 usual care patients (a baseline event rate of 107%) compared to 24 hospitalizations over a two-year period in 34 patients in the combined pilot clinic (event rate of 71%) resulting in a 33.6% reduction in events. We have based the current study power estimates on a 25% reduction in hospital admissions by the iCDM. We have chosen a more conservative effect of the iCDM as the iCDM is directed more at supporting patient self-management and monitoring, and does not involve direct medical management. Based on a 25% reduction in hospital admissions, and an alpha of 0.05, we have outlined the power given the following estimated event rates using the method of Demidenko E in the table below. We have provided a range of event rates as we do not have documented event rates from our targeted patient population. If the event rate is similar to that observed in our pilot clinic at St. Paul's Hospital, we will have sufficient baseline events for a power greater than 0.80 to detect an effect of 25% reduction in events.

| Usual Care* | iCDM* | Power |
|--------------------|--------------|--------------|
| 40%                | 30%          | 0.39         |
| 50%                | 38%          | 0.55         |
| 60%                | 45%          | 0.67         |
| 70%                | 53%          | 0.78         |

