**Additional Variables Assessed at Baseline:** *e-Health Literacy* will be assessed using the eHealth Literacy Scale (eHEALS) in all participants during their baseline assessment only. The eHEALS is used to assess the combined knowledge, comfort, and perceived skills at finding, evaluating, and applying electronic health information to health problems. *Depression* will be assessed using the Center for Epidemiologic Studies Depression scale. These data will be used as potential independent determinants to identify what patient characteristics are associated with improved outcomes.

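### The protocol lets observed baseline imbalance decide which covariates enter the primary model, through an open rule, so neither the estimated odds ratio nor its error rate is defined in advance

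*Protocol*

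**What the plan says.** The primary outcome (protocol, *Study Outcomes*) is the group difference in "hospital admissions from the time of randomization to the end of two years". Under *Statistical Analyses* it "will be modeled using ordered logistic regression with group assignment, age and sex as" covariates named in advance. The next sentence extends the same model: "In the event of potentially clinically relevant differences in baseline factors, we will include these covariates in the model". The candidates are given by example only: "such as socio-demographics, e-health literacy, depression, and other morbidities". The extended model is not labelled secondary or sensitivity, so as written it is the primary analysis.

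Three other places bear on this:

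- *Randomization* stratifies by sex and by recruitment site, meaning health authority. Only sex is then named for the model.
- *Baseline Assessment* lists what is collected: "We will collect the following data variables on all consenting participants: social demographics, medical history, current medications", followed by questionnaires and recent tests. Hospital admissions before randomisation are not named as an item.
- *Additional Variables Assessed at Baseline* gives e-health literacy and depression, two of the candidate covariates, a second use: "These data will be used as potential independent determinants to identify what patient characteristics are associated with improved outcomes".

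**The concern.** A rule that adjusts for whatever turns out unbalanced leaves three things unsettled.

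1. **Which model is primary.** Two analysts following the text could disagree on what counts as relevant and fit different models to the same data. If the choice were made with results visible, the test would no longer hold its nominal level.
2. **What is being estimated.** In a logistic model the treatment odds ratio is non-collapsible. Adding a prognostic covariate changes its value even when the arms are balanced, so the target depends on which covariates enter.
3. **Where precision comes from.** Adjustment helps most when the covariate predicts the outcome, whether or not it is unbalanced. Under this rule a strong predictor enters only if chance unbalances it.

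The omission of health authority is related: a factor used to stratify randomisation would reach the analysis only by the same accident.

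**Working it through.** **Inputs from the protocol.** 318 randomised and 15% drop-out: 318 × 0.85 = 270.3, which agrees with the stated 270 completers. Block sizes of 2, 4 and 6 imply 1:1 allocation, so 135 per arm. The level comes from *Sample Size Determination*: "Based on a 25% reduction in hospital admissions, and an alpha of 0.05". Sidedness is not stated; two-sided is assumed. The protocol gives no error-rate figure for the covariate rule, so there is none to reproduce. Its power table does not bear on this point and is not used.

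**Assumptions, because the protocol gives no values.** Four independent standard normal candidates; prognostic strength of 0, 0.3 or 0.6 log odds ratio per SD; imbalance cut-offs of 0.1 or 0.2 SD.

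**Step 1: how often would the rule be triggered?** The standardised difference between arms has standard error √(2/135) = 0.1217.

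- Cut-off 0.2 SD: 0.2/0.1217 = 1.643, two-sided probability 0.100 per covariate. For at least one of four: 1 − 0.900⁴ ≈ 0.345.
- Cut-off 0.1 SD: 0.1/0.1217 = 0.822, probability 0.411. For at least one of four: 1 − 0.589⁴ ≈ 0.88.

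Simulation agreed (about 35% and 88%). Whether the primary model is extended at all therefore turns largely on a cut-off that the protocol does not state.

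**Step 2: type I error.** Proportional-odds model, 270 patients, admissions grouped 0/1/2/3+, age and sex always included, no treatment effect, 4,000 trials per setting. Monte Carlo standard error: √(0.05 × 0.95/4000) ≈ 0.35 percentage points. Ranges run over the assumed strengths and cut-offs.

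| How the covariates are settled | Type I error at nominal 5% |
|---|---|
| Age and sex only, fixed | 4.7-5.8% |
| Age, sex and all four candidates, fixed | 4.9-5.5% |
| Fixed imbalance cut-off, blind to outcome | 3.9-5.3% |
| Cut-off picked after seeing results (none, 0.10, 0.15, 0.20 or 0.25 SD) | 5.7-7.8% |
| Covariates picked freely after seeing results (none, each alone, those unbalanced, all) | 6.2-11.2% |

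The last row depends strongly on prognostic strength: 6.2% at 0, 7.5-7.8% at 0.3, and 10.2-11.2% at 0.6.

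**Step 3: does the choice change the conclusion?** With no effect, the significance verdict differed between the age-sex model and the imbalance-adjusted model in 0.5-3.9% of trials. With a true log odds ratio of −0.5 and a 0.2 SD cut-off it differed in 4.6-7.6%.

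**Step 4: precision.** In those two settings with a true effect (2,000 trials each), power was as follows.

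| Model | Setting 1 | Setting 2 |
|---|---|---|
| Age and sex | 49.6% | 38.3% |
| Imbalance rule, 0.2 SD | 49.3% | 38.7% |
| All four candidates, fixed | 52.8% | 49.6% |

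The imbalance rule gained almost nothing over age and sex. Pre-specifying the same covariates gained about 3 and 11 points.

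**The case against.** **The trigger is baseline, not outcome.** This stands. Baseline data exist long before two-year outcomes, and a fixed rule applied blind to outcome does not inflate the error. A reader might infer that choosing covariates after seeing baseline differences in itself leaves the error uncontrolled. The simulation contradicts that.

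**The larger error rates describe conduct that the protocol does not describe.** This also stands. A separate simulation with eight candidates, each correlated 0.15-0.30 with outcome, gave 10-13% when the most favourable of several models was reported. A reader might take that as the expected error. It requires looking at treatment results before choosing, and the number and strength of the covariates are assumed. In that set-up a mechanical 0.1 SD rule gave 1-4%. Even the free-choice row above includes models that the rule does not license, such as a single covariate entered regardless of balance. The row closest to the text is the one where the cut-off is picked late.

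**Nothing says that outcomes will be in view.** True, but nothing prevents it. The stated blinding of investigators concerns interim results, the single-blinding concerns the coordinator who collects data, and no order is set between the covariate choice and the exploratory use of e-health literacy and depression.

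**Thresholds and timing belong in a statistical analysis plan.** Partly right. A plan that is not shown may close the rule, and its absence is no fault. The protocol is not silent, however: it places imbalance-driven adjustment inside the primary model.

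**Prior admissions may not be available.** This stands. They are not a named baseline item, and the hospital separations file is described for outcomes with no stated look-back.

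**Conclusion.** The point holds as a defect in how the primary model is fixed. It does not show that the error rate will be inflated. With a fixed rule applied blind to outcome, the level is about 4-5% or lower. Because the rule is open, the level cannot be stated in advance; under the assumed settings it is about 6-8% if the cut-off is picked on results and up to about 11% if covariates are picked freely on results. These figures rest on four assumed candidates and assumed prognostic strengths, and they bound what the wording permits without predicting what will be done.

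Three consequences need no misconduct: the odds ratio being estimated is not fixed in advance, prognostic information is used only when chance unbalances it, and health authority is omitted although it is a stratification factor. The documents give no data on how strongly the number of target diseases or prior admissions predicts admission in this population, so the power gains in the working illustrate the principle only. This is a worthwhile, inexpensive improvement and not a fatal flaw.

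**What to change.** - Pre-specify the primary model as group, age, sex, health authority and number of target chronic diseases. Health authority is known at randomisation and the number of diseases at eligibility, so neither needs new data collection.
- Add hospital admissions in the year before randomisation only if they can be obtained for all participants from the medical record or the provincial hospital separations file, and settle this before outcomes are seen.
- Move adjustment for observed baseline differences out of the primary model into a labelled sensitivity analysis.

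The cost is a change of wording and a few extra model terms. There are two small downsides: an unforeseen imbalance is addressed only in the sensitivity analysis, and prior admissions, if used, would need explicit extraction and possibly a look-back period in the provincial data request.

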After two years, the research coordinator will contact participants to inform them of their end of study follow-up assessment and assess adverse events similar to the one-year telephone contact above. This will consist of an assessment for secondary outcomes similar to the baseline assessment. Data on patient demographics, medical history, current medications, smoking status, and recent diagnostic and lab tests will be abstracted from the patient's physician's/nurse practitioner's medical record and confirmed by telephone with the patient. Questionnaires will be mailed to the patient with a stamped return envelope to mail back to the research centre with follow-up by the research coordinator as outlined above.

The research coordinators' roles will be limited to patient screening, participant recruitment, participant assessment and reporting of adverse events only. They will not be involved in delivering the iCDM intervention or in the care of the study participants.

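### SF-36 and heiQ are compared by an unadjusted t-test although baseline scores are collected: valid, but precision is given away at no saving

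*Protocol*

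**What the plan says.** The Statistical Analyses section gives one rule for all secondary outcomes: "Secondary outcomes between the two groups will be compared using the Pearson Chi-square test for categorical variables and independent samples t-test for continuous variables". It names covariates for the primary outcome only, which "will be modeled using ordered logistic regression with group assignment, age and sex as" prespecified covariates, with further baseline factors added to that model if clinically relevant differences appear. Between the two rules stands a general one: "Non-normally distributed continuous variables will be transformed prior to analyses".

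The Baseline Assessment paragraph lists what is collected from every consenting participant, including "social demographics, medical history, current medications, self-management and quality of life, smoking status". Of the two-year contact, Follow-up Assessments says: "This will consist of an assessment for secondary outcomes similar to the baseline assessment". So SF-36 and heiQ scores will exist in pairs. The Randomization paragraph stratifies by sex and by health authority.

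Study Outcomes adds "secondary outcomes of healthcare utilization such as length of hospital admissions, emergency room visits, physician/nurse practitioner visits, diagnostic and lab procedures".

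**The concern.** The first research question asks about both self-management outcomes and healthcare utilisation, so these secondary analyses carry much of what the trial will report.

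For the scales, the protocol collects a strong candidate predictor of the two-year score and then names a test that cannot condition on it. A t-test also leaves out the stratification factors; if sex or health authority is prognostic, this tends to overstate the standard error. The sample was set by feasibility ("We have identified a convenience sample of 318 participants as feasible"), so precision lost in the analysis cannot easily be bought back by recruiting more.

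The utilisation measures raise a narrower question. Anyone never admitted has zero hospital days. The transformation rule maps all those zeros to one single value, so the spike stays, and a t-test on the new scale no longer estimates a difference in mean days.

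**Working it through.** **Inputs from the protocol.** 318 randomised and 15% drop-out (Sample Size Determination); alpha 0.05; pilot usual-care admissions of 32 in 30 patients over two years.

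**Assumptions.** Equal arms (no ratio is stated; two arms in even-sized blocks), a two-sided test, a true difference of 0.30 SD, and a baseline to two-year correlation r of 0.3, 0.5 or 0.7. The protocol gives neither a correlation nor a target difference for any secondary outcome.

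**The plan's own figure.** 318 × 0.85 = 270.3, which reproduces the stated 270 completers, or 135 per arm. The protocol's power table concerns hospital admissions only and has no bearing here. Statistical Analyses expects 10% loss rather than 15%; the variance factors below do not depend on the sample size.

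**Formulas.** With the score variance set to 1 at both times, the between-patient variance v that enters the comparison is:

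- t-test on two-year scores: v = 1
- t-test on change scores: v = 2(1 − r)
- regression on the baseline score: v = 1 − r²

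Power = Φ(0.30 / √(2v/135) − 1.96), by normal approximation.

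For the t-test on two-year scores, √(2/135) = 0.1217, 0.30/0.1217 = 2.465, and Φ(0.505) = 0.69.

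| r | v, adjusted | cut in variance | power, two-year t-test | v, change | power, change t-test | power, adjusted |
|---|---|---|---|---|---|---|
| 0.3 | 0.91 | 9% | 0.69 | 1.40 | 0.55 | 0.73 |
| 0.5 | 0.75 | 25% | 0.69 | 1.00 | 0.69 | 0.81 |
| 0.7 | 0.51 | 49% | 0.69 | 0.60 | 0.89 | 0.93 |

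Confidence intervals narrow by 1 − √v against the two-year t-test: 5%, 13% and 29%. To match the adjusted analysis, that t-test would need 135/v = 148, 180 or 265 completers per arm.

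Against change scores at r = 0.7, the variance cut is 1 − 0.51/0.60 = 15%. Since 2(1 − r) − (1 − r²) = (1 − r)² ≥ 0, a change score never has the smaller variance, and below r = 0.5 it does worse than the two-year score alone.

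**Hospital days.** At the pilot rate, 32/30 = 1.07 admissions per patient. If admissions were Poisson, exp(−1.07) = 0.34 of usual-care patients would have none and so zero days. Overdispersion would raise this share (0.62 for a negative binomial with dispersion 3). The pilot came from a different clinic, and the protocol says event rates in its own population are undocumented, so this is an illustration.

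**Does the t-test break down on such data?** In simulations at 135 per arm, with assumed negative binomial counts and zero-heavy lognormal stays, its type I error was 0.044 to 0.051. For a 25% reduction in counts (dispersion 1), the t-test and negative binomial regression had near-equal power: 0.28 and 0.28 at mean 0.7, and 0.39 and 0.40 at mean 1.07. For length of stay, a t-test after log(1 + x) had power 0.19, 0.24 and 0.28 at mean admission rates of 0.4, 0.7 and 1.07, against 0.14, 0.18 and 0.22 untransformed.

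**The case against.** The strongest reply is that an unadjusted t-test is unbiased and valid in a randomised trial, that no secondary outcome has a power target, and that a statistical analysis plan, which may exist, could refine the method. Validity stands and sets the low severity. The last part does not remove the point, because the protocol does not leave the method open: it names a test that takes no covariate.

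The size of the gain is also open to challenge. It rests on an assumed correlation and is modest at 0.3. That stands, and the range is shown for this reason.

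A reader might go further in four ways that the text does not support:

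- **That the t-tests are on raw data.** The protocol says non-normal continuous variables will be transformed.
- **That two-year values are compared.** The protocol does not say whether two-year scores or change scores enter the test. At r = 0.7 the choice matters: the starting power is 0.69 or 0.89.
- **That the utilisation counts are mostly zeros.** This is stated nowhere. Many zeros are to be expected for hospital days and are plausible for emergency visits. Nothing supports it for physician visits or laboratory procedures in patients with two or more chronic diseases. Nor does the transformation rule necessarily fail for want of a logarithm of zero: no logarithm is named, and log(1 + x) is defined there.
- **That negative binomial regression should replace the t-test throughout.** The simulations show no loss of error control and essentially no power to gain for counts. Bed-days are not independent events, and a rate ratio is not a difference in days either. An offset for time at risk would help with unequal follow-up, but the choice of model is a trade-off.

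The unused-baseline argument also does not extend to utilisation, because the baseline list names no measure of prior use.

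**Conclusion.** The point holds for the scales that have a baseline value. The stated comparison is valid but less precise than the collected data allow. Against two-year scores the variance reduction is 9% to 49% for r between 0.3 and 0.7; if change scores were meant, it is 15% at r = 0.7. These figures assume 135 completers per arm, a two-sided 5% test and, for power, a 0.30 SD effect. They leave out any further gain from the stratification factors.

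For utilisation only a limited remark survives: a transformation cannot remove the spike at zero in hospital days, and a transformed-scale t-test does not estimate the difference in mean days. No false-positive risk was found, and the primary analysis is untouched. Severity is low.

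**What to change.** In Statistical Analyses, replace the t-test for SF-36 and heiQ by linear regression of the two-year score on group, baseline score, sex and health authority, reporting the adjusted mean difference with its confidence interval. Apply the same model to social support and EQ-5D-5L where a baseline value is collected; the baseline list does not name either, so this should be confirmed first. State how a missing baseline score is handled, since such participants would otherwise drop out of the regression.

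For hospital days, say which quantity is to be estimated, and do not rely on the transformation rule to deal with the zeros. Whether to use a count model, a two-part model or a comparison of means is for the trial statistician to decide.

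The cost is a change of wording before unblinding. For SF-36 and heiQ it needs no new data.
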